#### Exploratory outcomes

Exploratory outcomes are to assess whether the use of HS results in:A change in acid-base parameters and electrolyte levels as well as inflammatory/immune function indicesDifferences in clinical outcome comparators, including body composition analysis (water balance) using bioimpedance, need for renal replacement therapy, time on the ventilator, length of ICU and hospital stays, as well as ICU mortality and in-hospital mortality. We will also analyse 30-day and 90-day mortality.

### Study timetable

The timing of assessment of study parameters is outlined in Fig. 1.

### End of study

For included patients, the study will start with admission to the ICU and will end after day 6. Thereafter, patients will be followed up for secondary endpoints. Patients will not be monitored further if they are readmitted to the ICU.

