**Methods:**

In a prospective double-blind randomised controlled clinical trial, we aim to recruit 96 patients undergoing elective cardiac surgery for ischaemic and/or valvular heart disease. After postoperative admission to the intensive care unit (ICU), patients will be randomly assigned to receive 5 ml/kg ideal body weight HS (7.3% NaCl) or normal saline (NS, 0.9% NaCl) infused within 60 min. Blood and urine samples will be collected preoperatively and postoperatively up to day 6 to assess changes in renal, cardiac, inflammatory, acid-base, and electrolyte parameters. Additionally, we will perform renal ultrasonography studies to assess renal blood flow before, during, and after infusion, and we will measure total body water using preoperative and postoperative body composition analysis (bioimpedance). Patients will be followed up for 90 days.

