#### Secondary endpoints

Secondary endpoints are to investigate whether use of HS results in:Reduced cumulative vasopressor dose and shorter time on vasopressors after cardiac surgery- Differences in urinary output and postoperative weight gains between the two groups.

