### Statistics

Statistical evaluation will be conducted in the intent-to-treat population (carry forward last value method).

Descriptive presentation of the recorded data will be based on a scale type. Nominal/ordinal scales include cell frequencies at each level, missing data, valid number, and total number. Interval/proportional scales include arithmetic mean, standard deviation, median, spread, minimum, maximum, and valid number. In addition to the summary of the data using statistical parameters, descriptions will be provided individually for the total population as well as for both groups.

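### The instruction not to monitor patients further after ICU readmission makes no exception for clinical outcomes or vital status, and read literally it conflicts with the 90-day follow-up and the outcomes listed

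*Protocol article*

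**What the plan says.** End of study contains three statements in sequence. For included patients, "the study will start with admission to the ICU and will end after day 6". Next: "Thereafter, patients will be followed up for secondary endpoints". Then: "Patients will not be monitored further if they are readmitted to the ICU". The last statement has no time limit and no exception for any type of data.

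Other sections set out what is to be collected:

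- The Methods paragraph of the abstract: "Patients will be followed up for 90 days".
- Exploratory outcomes, under Outcome measures: "need for renal replacement therapy, time on the ventilator, length of ICU and hospital stays, as well as ICU mortality and in-hospital mortality", followed by "We will also analyse 30-day and 90-day mortality". The Objectives section gives the same list.
- Secondary endpoints: vasopressor dose and duration after surgery, with no stated end of window, and "Differences in urinary output and postoperative weight gains between the two groups".
- Primary endpoint: cumulative fluid given during the ICU stay. The section does not say whether a second stay counts.
- Statistics: analysis is in the "intent-to-treat population (carry forward last value method"), with no statement of which variables the carry-forward applies to.

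**The concern.** A patient who returns to the ICU can need renal support, ventilation or vasopressors there, can stay longer in hospital, and can die. These are the events that the exploratory list, and part of the secondary list, are meant to count. If site staff take the readmission sentence at its word, collection stops when such events become possible.

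Readmission occurs after randomisation and may itself be affected by the study fluid. Data lost from that point are therefore not missing at random with respect to outcome, and a comparison of the arms on the remaining data need not be fair. If last-value carry-forward were then applied to these outcomes, the gap would be filled with the patient's state before deterioration.

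The clinical outcomes, and mortality in particular, rest on few events in a trial of 96 patients, so a handful of unrecorded ones would matter to how the results are read.

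**Working it through.** **Step 1: the plan's own figure.** The only relevant calculation in the document is the sample size. Inputs from Estimation of sample size and Rationale for effect size: difference 1000 ml, SD 1734 ml, power 80%, α 0.05 (sidedness not stated).

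n per group = 2 × [SD × (z₀.₉₇₅ + z₀.₈₀) / difference]² = 2 × [1734 × (1.960 + 0.842) / 1000]² = 47.2, rounded up to 48.

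The stated 48 per group reproduces as a two-sided calculation; a one-sided one would give 38. It rests on fluid volume and does not depend on the readmission rule.

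**Step 2: the outcomes set against the readmission sentence.** Two readings are possible. On the literal reading, all study data collection ends at readmission. On the narrow reading, study measurements are not restarted in a second ICU stay but later follow-up goes on.

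| Outcome | Rank | Literal reading | Narrow reading |
|---|---|---|---|
| Fluid volume, first ICU stay | Primary | Complete | Complete |
| Vasopressor dose and time | Secondary | Cut off | Second stay unrecorded |
| Urine output, weight gain | Secondary | Cut off if readmitted while still being measured | Same |
| Renal replacement, ventilator time | Exploratory | Cut off | Second stay unrecorded |
| Hospital stay, in-hospital mortality | Exploratory | Cut off | Retained |
| 30-day and 90-day mortality | Exploratory | Cut off | Retained |

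The literal reading contradicts the 90-day follow-up and the mortality outcomes. The narrow reading removes that contradiction but still loses organ-support data from a second stay.

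**Step 3: a second mismatch in the same section.** Follow-up after day 6 is described as serving secondary endpoints. The secondary list contains no mortality outcome; mortality is exploratory. As worded, the sentence does not cover the outcomes that need follow-up to day 90.

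**Step 4: illustration of size.** The document gives neither a readmission rate nor a mortality rate, so every rate here is an assumption: readmission r = 2%, 5% or 10%; 90-day mortality m₀ = 2% in patients not readmitted; m₁ = 10% to 30% in those readmitted. It takes the literal reading and counts every death after readmission as unrecorded.

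Unrecorded deaths = 96 × r × m₁. Other deaths = 96 × (1 − r) × m₀. Share missed = unrecorded / (unrecorded + other).

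| r | Readmitted (96 × r) | Other deaths | Unrecorded, m₁ = 10% | Share | Unrecorded, m₁ = 30% | Share |
|---|---|---|---|---|---|---|
| 2% | 1.9 | 1.88 | 0.19 | 9% | 0.58 | 23% |
| 5% | 4.8 | 1.82 | 0.48 | 21% | 1.44 | 44% |
| 10% | 9.6 | 1.73 | 0.96 | 36% | 2.88 | 62.5% |

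Under these assumptions, 0.2 to 2.9 deaths would be missed across both arms. The split between arms, and so the direction of any bias, cannot be derived.

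**The case against.** The strongest reply is that the sentence speaks of monitoring, not of follow-up, and that the sentence before it uses the other term. Elsewhere the article uses monitoring for bedside observation (Study conduct) and for the clinic's data system (Data management). On that view the rule means only that study measurements are not restarted in a second ICU stay, and 90-day mortality is collected as promised. This reading is possible, but the article does not state it. The sentence comes straight after the one on later follow-up, which makes it easy to take as a limit on that follow-up. Even on the narrow reading, ventilator, renal replacement and vasopressor data from a second stay go unrecorded.

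A second reply is that Fig. 1 and the full protocol are not at hand and may settle the matter. That would answer a complaint about missing detail. Here the article states a rule, and the rule as worded conflicts with its own outcome list.

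Some stronger conclusions are tempting, and the objection to them stands:

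- **That the sickest patients are removed, or intention-to-treat is breached.** No exclusion or withdrawal at readmission is stated, and the analysis population is intention-to-treat. The issue is missing data.
- **That patients who die after readmission will be analysed as alive.** Carry-forward is mentioned once, in a parenthesis, and is not said to apply to vital status. Statistics also promises counts of missing values for nominal data, so a gap should at least be visible.
- **That the primary endpoint is biased.** Fluid in the first stay is complete before any readmission, and limiting the endpoint to that stay is a legitimate choice. Care providers are also blinded, so discharge cannot be steered by known allocation.
- **That harm from hypertonic saline would be hidden.** Nothing in the document indicates that readmission differs by arm, or in which direction.

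**Conclusion.** The point holds as a conflict in the text with a real consequence for data collection. Followed literally, the readmission sentence cannot be carried out together with the 90-day follow-up and the listed clinical and mortality outcomes, and it can truncate secondary endpoints. Because readmission follows randomisation and may depend on treatment, the resulting gaps would be informative, and carry-forward would make this worse if it were applied to these outcomes.

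The reach is limited. The outcomes at risk are secondary or exploratory; the first-stay fluid volume and the sample size are untouched. The range of 0.2 to 2.9 missed deaths rests wholly on assumed rates and on the literal reading, and the size and direction of any bias between arms cannot be determined from the document. This should be corrected, but it does not undermine the primary comparison.

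**What to change.** Replace the readmission sentence with wording such as:

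> On ICU readmission only study-specific procedures (renal ultrasound, bioimpedance, extra sampling) stop; renal replacement, ventilation, vasopressor use, fluids, hospital stay and 30-/90-day vital status are still collected for every randomised patient.

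Two further edits belong with it:

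1. Under Primary endpoint, state that it covers the index ICU stay, and report fluids given during any readmission separately.
2. Under End of study, reword the purpose of follow-up after day 6 so that it includes the exploratory mortality outcomes as well as the secondary endpoints.

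The cost is a few sentences and a little more extraction from routine records. The trial runs at one centre whose patient monitoring system already records data electronically, and the change affects what is collected, not how patients are treated.

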### Statistics

Statistical evaluation will be conducted in the intent-to-treat population (carry forward last value method).

Descriptive presentation of the recorded data will be based on a scale type. Nominal/ordinal scales include cell frequencies at each level, missing data, valid number, and total number. Interval/proportional scales include arithmetic mean, standard deviation, median, spread, minimum, maximum, and valid number. In addition to the summary of the data using statistical parameters, descriptions will be provided individually for the total population as well as for both groups.

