### Outcome measures

#### Primary endpoint

The primary endpoint is the difference in total cumulative fluid volume administered during ICU stay between patients receiving HS and patients receiving NS following elective cardiac surgery.

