### Premature study termination

The sponsor or investigator may terminate the study prematurely for a variety of reasons, including unforeseen ethical concerns, insufficient participant recruitment, doubts about the safety of the participants, or alterations in accepted clinical practice that make the continuation of a clinical trial unwise. For patients already enrolled in the study, treatment will be stopped immediately, while patient data will be recorded and observed until the patient leaves the ICU.

If the study has to be terminated prematurely, the regulatory authorities will be informed within 15 days.

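### Carrying the last value forward adds zero fluid to an incomplete cumulative total, and the protocol gives two different recording windows for that total

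*Protocol article*

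**What the plan says.** The Statistics section of the protocol article states: "Statistical evaluation will be conducted in the intent-to-treat population (carry forward last value method". No endpoint is exempted.

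Under Primary endpoint, the quantity compared is "the difference in total cumulative fluid volume administered during ICU stay between patients receiving HS and patients receiving NS". It is a cumulative sum whose window is the ICU stay, with no upper day limit. Statistical methods assigns it the Mann-Whitney U test.

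End of study gives a different window: "For included patients, the study will start with admission to the ICU and will end after day 6". It continues: "Thereafter, patients will be followed up for secondary endpoints". The primary endpoint is not mentioned there. It adds: "Patients will not be monitored further if they are readmitted to the ICU".

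Premature study termination is the one place that ties recording to the ICU stay ("patient data will be recorded and observed until the patient leaves the ICU"), and it applies only if the trial is stopped early.

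**The concern.** Carry-forward assumes that a measurement would have stayed at its last level. For a running total, that means the patient received no more fluid, which cannot be right for someone still being treated in the ICU. The error for that patient has one sign: the total is too low.

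Two groups are exposed. The first is patients who withdraw during the ICU stay. The second is patients still in the ICU after day 6, if fluid recording ends with the study, as End of study suggests. Long-stay patients are plausibly among those who receive most fluid, so the rule could move some of the highest totals into the middle or lower ranks of a rank test. The readmission rule raises a related question, because the protocol does not say whether fluid given on a return to the ICU belongs to the endpoint.

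At stake is whether the primary difference means what the protocol says it means. If incomplete totals are more common in one arm, that arm appears to have used less fluid than it did.

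Daily body weight has a milder form of the problem: carry-forward freezes weight at the last measurement and ignores any later change.

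**Working it through.** **The plan's own figure.** Inputs from Estimation of sample size and Rationale for effect size: mean 3381 ml, SD 1734 ml, target reduction 1000 ml, power 80%, α 0.05 (two-sided assumed; it reproduces the stated figure).

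n per arm = 2 × (1.960 + 0.842)² × 1734² / 1000² ≈ 47.2, rounded up to 48. Power at 48 per arm is 80.7% by the normal approximation and 79.9% by the t-test. The planned 48 per arm is reproduced, so sample size is not at issue.

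**Inputs the protocol does not give.** These are the share of patients in each arm whose total is cut short, and how much of the total is lost. Assumption: affected patients keep 50% of their true total. Shares of 0% to 10% per arm are examined.

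**Affected patients are a random subset.** With no true effect,

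shift in the mean difference = (difference in shares) × (fraction lost) × mean.

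- 5% against 0%: 0.05 × 0.5 × 3381 = 85 ml
- 10% against 0%: 0.10 × 0.5 × 3381 = 169 ml

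**Simulation.** Gamma-distributed totals with the protocol's mean and SD, 48 per arm, Mann-Whitney U test, 4000 runs per setting. Differences are HS minus NS.

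| True effect | Share cut, HS / NS | Random patients | Highest-volume patients |
|---|---|---|---|
| 0 | 10% / 10% | −2 ml | +6 ml |
| 0 | 5% / 0% | −73 ml | −168 ml |
| 0 | 10% / 0% | −166 ml | −351 ml |
| 0 | 0% / 10% | +171 ml | +348 ml |
| −1000 ml | 10% / 10% | −959 ml | −958 ml |
| −1000 ml | 10% / 0% | −1109 ml | −1317 ml |
| −1000 ml | 0% / 10% | −838 ml | −645 ml |

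The simulated 73 ml sits a little below the exact 85 ml. The Monte Carlo standard error is 1734 × √(2/48) / √4000 ≈ 6 ml, so the gap is about two standard errors. The range of about 70 to 350 ml is 7% to 35% of 1000 ml.

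For equal 10% shares under a true 1000 ml effect, the exact result for random patients is 1000 × (1 − 0.10 × 0.5) = 950 ml, a shrinkage of 5%. The simulated values of 958 and 959 ml give about 4%.

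**Error rate.** With no true effect and 10% against 0%, the two-sided rejection rate is 8.3% (random) to 12.6% (highest-volume), against 5.3% with no cut-offs. The 12.6% should be read with care. Equal 10% shares among the highest-volume patients also gave 10.7% with no mean bias, because that setting cuts a fixed number of top values within each arm. A cut at one common volume in both arms leaves the test at its nominal level.

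**The case against.** The strongest reply is that this merges several mechanisms and that bias is not shown. Most of it stands, and it rules out four readings that a reader might reach.

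- **ICU discharge is not a missing-data problem.** A discharged patient has a complete total under the endpoint as defined, and nothing is imputed. Only withdrawal during the stay, or a stay outlasting the recording, is affected.
- **ICU death is not scored low by carry-forward.** Fluid given up to death is the observed value of the endpoint. An early death may then rank as a low-fluid result, but that follows from the endpoint definition, and deleting carry-forward would not change it.
- **Readmission fluid is not shown to be wrongly lost.** It goes uncounted because of the monitoring rule, and that is an error only if the ICU stay was meant to include readmissions. The Primary endpoint section leaves this open.
- **Bias towards HS is not established.** It needs an imbalance between arms, and the sign reverses if the affected patients are in the NS arm. A more extreme simulation (lognormal totals, no true effect) cuts the three or five highest-volume HS patients to 1000 ml and no NS patients; the test then favours HS in 17% or 37% of trials, against a nominal 2.5%. That is a one-arm extreme. With the same cut in both arms the difference is about 0 ml.

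It is also fair to say that truncation at day 6 is inferred. Study parameters says all fluids and cumulative amounts are documented, Monitoring describes real-time capture, and the timing figure is not available here. The population is elective with several exclusions, so few patients may be affected.

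What the reply does not remove is that carry-forward is stated for the whole evaluation and is unsuitable for a running sum. The two windows also disagree as written. This is a rule the protocol fixes badly, not a detail left to a statistical analysis plan.

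**Conclusion.** The concern holds in this limited form. Carry-forward imputes zero further fluid for any patient whose recording stops while still in the ICU, so that patient's total is understated. The Primary endpoint and End of study sections give windows that do not match and must be reconciled.

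Bias in the comparison is a risk, not a demonstrated fact. If affected patients keep half their total and the arms differ by 5 to 10 percentage points, the shift is about 70 to 350 ml in either direction. The lower end assumes random patients at 5 points, and the upper end the highest-volume patients at 10 points. With equal shares there is essentially no bias under no effect, and modest shrinkage of a true effect. The shares and the fraction lost are assumptions, since the protocol gives neither.

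**What to change.** 1. Delete carry-forward for the cumulative fluid endpoint.
2. Reconcile Primary endpoint and End of study to one recording window for all patients: for example ICU admission to a fixed day, or ICU admission to ICU discharge with recording continued past day 6. State whether readmission fluid within that window counts.
3. Analyse observed totals, with multiple imputation for the few that remain incomplete.
4. Analyse daily weight with a mixed model on observed values in place of carry-forward.
5. Report a sensitivity analysis that gives ICU deaths the worst rank. This fits the planned Mann-Whitney test, but it turns the endpoint into a composite of fluid and death, so it should not replace the primary analysis.

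The sample size stays at 48 per arm and no visits are added. The cost is slightly more data extraction, from a monitoring system that already records in real time, and some extra analysis work. The change should be made before unblinding.

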#### Statistical methods

This is a classic two-group study with parallel groups. Whether HS results in less total fluid volume will be assessed by the Mann-Whitney *U* test. Interval variables between groups will be compared using Student’s *t* test or the Mann-Whitney *U* test as appropriate. Fisher’s test for exact probability will be used for the nominal scale data. In the event of an uneven baseline situation, multivariable regression (linear regression for interval outcomes and logistic regression for dichotomous outcomes) will be used for adjustment of baseline differences.

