### Randomisation and blinding

All patients undergoing cardiac surgery and meeting the eligibility criteria as defined above will be enrolled in the study and randomised to either the HS group (7.3% NaCl) or the NS group (0.9% NaCl). Computerised randomisation using a variable block size [2, 4, 6] will be performed by a member of the study team not involved in any part of treatment (neither nurse, resident, nor supervisor). A box with the study vials and study infusion will be given to the treating intensive care physician with the patient’s number in the study. Participants, care providers, investigators, and outcome assessors will be blinded to study group assignment. A list for emergency un-blinding of the study will be held by a designated study quality manager.

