### Study parameters

We will obtain baseline data (age, gender, height, weight, BMI), baseline comorbidities, risk scores, and preoperative and postoperative routine laboratory parameters in all patients. Additionally we will perform sonographic assessment of renal blood flow and assess body composition (bioimpedance) at predefined endpoints.

All types of fluids and the cumulative amounts (blood products included), daily body weight, and cumulative doses of medication will be documented. Furthermore, the need for renal replacement therapy, length of mechanical ventilation, length of ICU and hospital stays, and mortality will be assessed.

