#### Estimation of sample size

Sample size calculation was based upon fluid data from the Hemacetat study (NCT02895659) [28], conducted at our institution with the same patient collective. Preliminary data showed that patients received a mean of 3381 ml fluid during their ICU stay, with a standard deviation of 1734 ml. A clinically relevant effect size was determined to be a reduction of 1000 ml fluid (30%).

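### Covariate adjustment is triggered by chance baseline imbalance instead of being fixed in advance, and its role beside the primary Mann-Whitney test is unclear

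*Protocol article*

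**What the plan says.** All under the protocol article's own headings:

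- **Primary endpoint:** "The primary endpoint is the difference in total cumulative fluid volume administered during ICU stay", compared between the hypertonic and normal saline groups.
- **Statistical methods, primary test:** "Whether HS results in less total fluid volume will be assessed by the Mann-Whitney" U test. No condition is attached.
- **Statistical methods, last sentence:** "In the event of an uneven baseline situation, multivariable regression" is to be used to adjust for baseline differences, specified as "linear regression for interval outcomes and logistic regression for dichotomous outcomes". The sentence gives no definition of uneven and no covariate list. It does not say whether the regression replaces the tests named before it or supports them.
- **Study parameters:** "We will obtain baseline data (age, gender, height, weight, BMI), baseline comorbidities, risk scores" and routine laboratory values, in all patients.
- **Randomisation and blinding:** "Computerised randomisation using a variable block size [2, 4, 6] will be performed". No stratification factor is stated.
- **Estimation of sample size:** "patients received a mean of 3381 ml fluid during their ICU stay, with a standard deviation of 1734 ml", with a target reduction of 1000 ml. The calculation uses this raw SD and takes no credit for covariates.

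Total volume in ml is an interval outcome, so the conditional sentence covers the primary endpoint as well as the others.

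**The concern.** In a properly randomised trial, an observed baseline difference is a chance event. Its size says nothing about whether the variable predicts fluid volume, and that is what decides whether adjustment is worthwhile. A trigger based on imbalance therefore selects the wrong variables: it can bring in an irrelevant covariate because it differs by chance, and omit a prognostic one because it is balanced.

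Two things are at stake. First, someone must judge after the data are in whether the baseline is uneven and what to adjust for, so the adjusted result is open to discretion. It is also on a different footing from the primary test, being a difference in means and not a rank comparison, and the text does not say how a reader should weigh the two. Second, the precision available from covariates collected in every patient is mostly not used.

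This goes beyond detail left to a statistical analysis plan. Such a plan could define uneven and list candidate variables, but the protocol has already committed to imbalance as the trigger.

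**Working it through.** **1. The plan's own figure.** Inputs from Estimation of sample size and Rationale for effect size: difference 1000 ml, SD 1734 ml, α 0.05 (taken as two-sided), power 80%.

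n per arm = 2 × (1.960 + 0.842)² × (1734/1000)² = 47.2, so 48. The stated 48 per group reproduces. Power at 48 per arm is 80.7% by the normal approximation and 79.9% by the exact t test. One-sided α 0.05 would give 38 per arm and does not match.

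**2. How often chance alone fires the trigger.** The protocol states no threshold. Assuming a rule of p < 0.05 on k independent variables, the probability is 1 − 0.95^k: 14% for k = 3, 23% for k = 5 (22% to 23% in simulation) and 40% for k = 10. Height, weight and BMI are correlated, as are comorbidities and risk scores, so figures for large k are illustrative only.

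**3. What fixed adjustment could gain (normal approximation).** Residual SD = 1734 × √(1 − R²), where R² is the share of outcome variance explained by the covariates. The protocol gives no R², so a range is shown.

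| Assumed R² | Power at 48 per arm | n per arm for 80% |
|---|---|---|
| 0 | 80.7% | 48 |
| 0.05 | 82.6% | 45 |
| 0.10 | 84.6% | 43 |
| 0.20 | 88.5% | 38 |

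**4. Simulation with normal data.** 48 per arm, five independent covariates sharing R² equally, uneven taken as any baseline t test with p < 0.05, 6000 runs per setting. The conditional rule is modelled in its strongest form: the regression on the uneven covariates replaces the Mann-Whitney test whenever the trigger fires.

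| Assumed R² | Mann-Whitney | Conditional rule | Always adjusted | Type I error, conditional rule |
|---|---|---|---|---|
| 0 | 78.5% | 78.5% | 77.6% | 5.1% |
| 0.10 | 78.1% | 78.0% | 81.8% | 4.7% |
| 0.20 | 78.6% | 79.6% | 86.0% | 4.3% |
| 0.30 | 77.9% | 79.2% | 89.9% | 4.1% |
| 0.40 | 77.8% | 79.5% | 94.1% | 3.4% |

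At R² 0.20, always adjusting gains 86.0 − 79.6 = 6.4 points over the conditional rule and 86.0 − 78.6 = 7.4 over Mann-Whitney alone. At R² 0.05, step 3 gives 82.6 − 80.7 = 1.9 points. At R² 0 it loses 78.5 − 77.6 = 0.9 points. If the smaller of the two p-values were reported, type I error would be 4.7% to 5.6%.

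**5. Skewed data.** Assume lognormal control volumes with mean 3381 and SD 1734 ml, a 1000 ml shift, three covariates and R² from 0 to 0.3. Mann-Whitney has about 92% power. Always-adjusted linear regression on raw ml has about 79% to 90%. Covariate adjustment on the rank scale has about 91% to 97%. The scale of the adjusted analysis therefore matters as much as the adjustment itself.

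**6. Does weight-based dosing make body weight a strong predictor?** The study infusion is 5 ml/kg. With an assumed SD of dosing weight of 10, 15 or 20 kg, it contributes an SD of 50, 75 or 100 ml. As a share of 1734² this is 0.08%, 0.19% or 0.33%. Dosing alone explains almost nothing.

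**The case against.** The strongest reply is that the primary test is fixed. The Mann-Whitney test is named for total volume without condition, the regression sentence comes after the tests for all other variables, and it nowhere claims to replace anything. On the natural reading it is a supportive analysis whose details a statistical analysis plan could supply. A reader might infer that the primary model itself is chosen from the data, or that two rival primary results would compete. The text does not support that. It leaves the role of the regression open, which is a narrower fault. A reader might also expect a raised false-positive rate, but step 4 shows no material inflation.

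Other parts of the reply also stand. R² is unknown, and total volume has no baseline value of its own, so R² may be modest. The power comparison in steps 3 and 4 rests on normal data. With skewed data, moving the primary analysis to regression on raw ml could lose power against Mann-Whitney. Choosing a log scale only if the data look skewed would be another data-driven choice, and it would turn a 1000 ml difference into a ratio. Weight-based dosing is no argument for a high R².

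The reply does not rescue the trigger. Even as a supportive analysis, an adjustment that appears only when chance imbalance is noticed, with covariates chosen by that imbalance, is open to discretion and poorly aimed. Defining uneven more precisely would leave that unchanged.

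**Conclusion.** The point holds in this form: adjustment depends on chance imbalance, balanced prognostic variables are dropped, and the standing of the adjusted result beside the primary Mann-Whitney test is not stated. The harm is discretion over that result and lost precision; the error rate is not at issue.

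With normal data and 48 per arm, the precision forgone is worth roughly 2 to 7 points of power for R² between 0.05 and 0.20, and nothing if the covariates are not prognostic. These R² values are assumptions, as are the p < 0.05 trigger and the independent covariates in the simulation. With skewed data the gain appears on the rank scale but not on raw ml. The change is worth making because it is almost free. The fault does not undermine the planned primary test or the sample size.

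**What to change.** Replace the conditional sentence under Statistical methods as follows.

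1. Delete the imbalance trigger.
2. Name in advance a few baseline covariates expected to be prognostic and already collected, for example age, preoperative risk score and body weight. Adjust for them whatever the observed balance.
3. Fix one scale for the adjusted analysis before unblinding, with no rule that depends on how skewed the data turn out to be.
4. State one primary analysis. Either keep the unadjusted Mann-Whitney test as primary with the fixed-covariate regression as supportive, or make a rank-based covariate-adjusted test primary with Mann-Whitney as sensitivity analysis. The first option removes the ambiguity but does not recover power in the primary test; the second can do both.
5. Always adjust postoperative weight gain for preoperative weight.

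The cost is wording, settled before unblinding. No new data or patients are needed, and 96 stands. The downside is about 1 point of power in the adjusted analysis if the chosen covariates turn out not to be prognostic.
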